## Abstract

**Background:**

What we eat as infants and children carries long-term consequences. Apart from breastfeeding, the composition of the complementary diet, i.e. the foods given to the infant during the transition from breast milk/infant formula to regular family foods affects the child’s future health. A high intake of protein, a low intake of fruits, vegetables and fish and an unfavorable distribution between polyunsaturated and saturated fats are considered to be associate with health risks, e.g. obesity, type 2 diabetes and dyslipidemia later in life.

**Methods:**

In a randomized, controlled study from 6 to 18 months of age we will compare the currently recommended, Swedish complementary diet to one based on Nordic foods, i.e. an increased intake of fruits, berries, vegetables, tubers, whole-grain and game, and a lower intake of sweets, dairy, meat and poultry, with lower protein content (30% decrease), a higher intake of vegetable fats and fish and a systematic introduction of fruits and greens. The main outcomes are *body composition* (fat and fat-free mass measured with deuterium), *metabolic and inflammatory biomarkers* (associated with the amount of body fat) in blood and urine, *gut microbiota* (thought to be the link between early diet, metabolism and diseases such as obesity and insulin resistance) and *blood pressure*.

We will also measure the participants’ energy and nutrient intake, eating behavior and temperament through validated questionnaires, acceptance of new and unfamiliar foods through video-taped test meals and assessment of cognitive development, which we believe can be influenced through an increased intake of fish and milk fats, notably milk fat globule membranes (MFGM).

**Discussion:**

If the results are what we expect, i.e. improved body composition and a less obesogenic, diabetogenic and inflammatory metabolism and gut microbiota composition, a more sustainable nutrient intake for future health and an increased acceptance of healthy foods, they will have a profound impact on the dietary recommendations to infants in Sweden and elsewhere, their eating habits later in life and subsequently their long-term health.

**Trial registration:**

NCT02634749. Registration date 18 December 2015.

## Background

Early feeding affects health and development later in life [1]. The positive effects of breastfeeding are well known [2], but less is known about how different types and timing of introduction of complementary foods, i.e. the foods used during the transition from breastfeeding or formula-feeding to family foods affect short- and long-term health [3]. From around 4–6 mo. of age eating habits of infants start to change from a liquid diet of breast milk or infant formula to a more diversified diet, mixing breast milk or formula with increasing amounts of solid foods, ending with the child eating the same food as the rest of the family. During this time of complementary feeding, demands for energy and nutrients remain high, especially during the second half of the first year of life. We and others have shown a link between protein intake during this time period and later risk for overweight [4, 5]. Current dietary recommendations for infants and children suggest lower protein intake compared to previous guidelines [6]. Further, we and others have shown that higher intakes of polyunsaturated fatty acids and lower intakes of saturated fatty acids in the diet of infants improve the blood lipid profile and lower blood pressure, and that these influences track into childhood [7–10]. These polyunsaturated fatty acids, especially in the long-chain form (LCPUFA) found in fish and fish oils have in some studies also been associated with lower risk of asthma, atopic disease and infections during infancy and childhood [11–13].

The composition of the complementary food is important also from the perspective of flavour, texture and presentation [14]. Already the foetus experiences different sensations of flavour through the amniotic fluid, reflecting what the mother eats [15]. Through breast milk, this exposure continues as infants encounter different flavours in the milk, depending on the types of food the mother consumes [15]. These processes prime the newborn infant to accept the same types of foods as the mother usually takes, including flavours outside the normal preferences of the infant, i.e. sweet, salty and fatty [16]. Further, the acceptance of different textures of foods changes during infancy. As the oral motor skills of the infant develop, the child is able to handle increasingly lumpy and solid foods. A normally developing infant will have periods of greater acceptance of novel foods both in terms of taste and texture, usually coinciding with the time when complementary foods are introduced [17]. However, this window of opportunity to introduce new foods begins to close, usually around 10–12 mo. of age, when the child grows increasingly suspicious of unfamiliar tastes, i.e. develops food neophobia, but also, if solids have not been introduced at this time, to the texture of common food items. This reluctance to try new food items particularly applies to fruits and vegetables, which have a bitter and sour tastes and need repeated exposures to be learned to be appreciated [18]. Numerous studies have shown that fruits and vegetables are an important part of healthy eating habits during all ages [19], but that the actual intake of these food items among young children is low and the best ways to increase the intake largely unknown [20]. Population-based studies from Sweden and elsewhere have shown that the dietary intake of children is not satisfactory from a public health perspective, with intakes of refined sugars, fatty foods and salt being too high and intakes of fruits and vegetables being too low [21]. A recent report on food habits of Swedish adults from the National Food Agency found the worst food habits among young adults age 18–30 years, especially among young women [22]. This is of concern as this is the age when people start families and possibly transmit their poor eating habits to their children.

The New Nordic Food programme [23] is an initiative that highlights the health, gastronomic and sustainability aspects of foods produced within the Nordic region [24]. The overall aim of the diet is to: a) allow a higher energy intake from plant foods and a lower energy intake from meat, b) consume more sea and lake foods and c) consume more foods from the rural countryside [25]. Compared to the regular Swedish diet, the Nordic diet (ND) stresses higher intakes of regionally produced fruits, berries, vegetables, tubers, and legumes as well as higher intakes of whole-wheat, vegetable fats and oils, fish and egg, and lower intake of sweets, desserts and dairy, meat and poultry products, but at the same time being in line with current dietary recommendations [26]. In adults, studies on ND have shown beneficial effects on weight and metabolic and cardiovascular disease biomarkers of the same magnitude as the Mediterranean diet [27, 28] as well as on total mortality [29]. The diet has also been evaluated in a large intervention study among Danish school children aiming to improve dietary intake, nutrient status, growth, early risk biomarkers for adult chronic disease, well-being and cognitive function [30, 31]. The results show an improved dietary intake including higher intakes of fish and vegetables [31] and metabolic effects such as a decrease in mean arterial blood pressure, decreased total cholesterol and improved insulin resistance [32, 33].

Differences in eating behaviour among infants and children is an issue that influence the risk of future obesity [34]. These patterns evolve already in infancy, where genetic predisposition, e.g. sensitivity to bitter taste [35] combine with natural responses to foods and flavours, actual food exposure and parental feeding practices to form the eating style of the individual [36]. Behavioural patterns in childhood that have specifically linked to later obesity include internal factors such as high enjoyment of food, high food responsiveness, emotional overeating and low responsiveness to internal satiety cues, e.g. high eating speed and low satiety sensitivity and external factors such as parental restriction. These behaviours are important to include when examining effects of different diets on later health outcomes and can be measured by validated questionnaires [37–39].

The nutrient intake of the infant affects its development, for example an adequate iron intake during the second half year of life increases psychomotor development compared to infants not receiving iron supplementation [40]. Systematic reviews of studies on supplementation with LCPUFAs to healthy term infants have failed to show effects on cognitive development measured with the standardized tests such as Bayley Scales of Infant Development (BSID) [41, 42]. However, in even quite small interventions of LCPUFAs during infancy, using more specific tests of brain development has shown positive both short- and long-term effects [43, 44]. Also, a recent randomized, controlled intervention study supplementing infant formula with bovine milk fat globule membranes (MFGM) found a significant effect on cognitive development [45]. It is of note, that the methodology to measure cognitive and psychomotor development following nutritional interventions in infancy using the BSID has recently been challenged, calling for more sensitive methods, including for example attention free play [46].

The gut microbiota has attracted increasing attention during the last several years as a key player in the pathophysiology of chronic disease [47, 48]. Effects on faecal microbiota composition has been a proposed pathway linking early dietary intake with later metabolic outcomes [49] and the development of overweight and also allergic diseases [50]. With the transition from breast-feeding to complementary feeding the gut microbiota undergoes significant changes where correlations have been found between infancy body mass index (BMI) and the faecal flora [51].

In the present study, we draw from the research outlined above, aiming to improve body composition, metabolic markers, cognitive development, blood pressure, food acceptance and the faecal microbiota composition of young children by using a protein-reduced, ND as a basis for complementary feeding.

## Methods/Design

The overall aim of the study is to compare the effects of a protein-reduced, Nordic diet (ND) portfolio intervention on body composition, metabolic and inflammatory markers, blood pressure, cognitive development, food acceptance and faecal microbiota composition to conventional complementary feeding from 6 to 18 months of age.

More specifically, we will investigate if a complementary diet:Lower in protein (total reduction 30%) from 6 to 18 mo. of age will affect growth, body composition, i.e. reduce total body fat mass and improve metabolic markers, i.e. decrease plasma (P-) levels of insulin, glucose and insulin-like growth factor 1 (IGF-1)Based on Nordic foods from 6 to 18 mo. of age will affect growth, body composition, i.e. reduce body fat mass and improve metabolic markers and the faecal microbiota composition, i.e. a microbiota composition associated with less obesity and inflammationWith a modified fat intake, i.e. a higher intake of long-chain polyunsaturated fatty acids and milk fats, including MFGM will improve body composition, blood pressure, metabolic markers including erythrocyte fatty acid composition, cognitive development and the faecal microbiota compositionWith a systematic introduction of plant foods from the Nordic diet during weaning will increase the acceptance of a larger variety of fruits, berries and vegetables into the diet of the young child at 12 and 18 mo. of age

Primary and secondary outcomes of the study and variables collected on adherence and background factors are shown in Table 1.

**Table 1 Tab1:** Primary and secondary outcomes and adherence and background factors collected the Optimized complementary feeding study

Primary outcomes	
Body composition	Anthropometry (body weight, body length, head circumference) Fat and fat-free mass (deuterium-labelled water)
Biomarkers of metabolic function	P-insulin, P-glucose, P-IGF-1, P-lipids and lipoproteins, P-fatty acids and erythrocyte membrane fatty acids including LCPUFAs (DHA, EPA, ARA), metabolomics (plasma and urine) and lipidomics (plasma), markers of oxidatative capacity, hsCRP
Faecal microbiota composition	Obesity-promoting microflora
Blood pressure	
Secondary outcomes, adherence and background factors	
Dietary intake	
Biomarkers of adherence	Haemoglobin, iron status, P-urea, vitamins C, A, E, carotenoids, folic acid, C15 and C17 fatty acids
Food acceptance	Videotaped test meal
Eating behaviour	CEBQ, CFQ, COC, bitter taste gene *TAS2R38*
Temperament	BBQ and TBQ
Cognitive development	Attention free play and ASQ
Allergy and atopic manifestations	
Symptoms registration	
Background factors	Child’s neonatal history, early nutrition, past and present illnesses, family composition, mother’s pregnancy history, education, employment, smoking habits, history of chronic illnesses, father’s education, employment, smoking habits, history of chronic illnesses

### Participants and recruitment

Through invitation-letters sent to all infants in Umeå municipality at 3 mo. of age, healthy, full-term singletons will be recruited. When parents consider it appropriate to introduce complementary foods into the diet of their child, but no later than at 6 mo. of age, the child will be randomly allocated to one of two study groups, i.e. the Nordic diet group (intervention, ND) or the Regular diet group (control).

#### Inclusion criteria

Healthy, singleton infants 4–6 mo. of age> 37 weeks of gestation at birthBirth weight > 2500 gAvailable throughout the study period, i.e. the participant will remain in the study area (Umeå municipality) and will not commence childcare outside the home during the extent of the study, i.e. until 18 mo. of age.Parents or legal guardians are able to give written informed consent to participation in the study.

#### Exclusion criteria

Children with chronic illnesses that will affect feeding or growth, including food allergies or intolerance to study productsIntake of any complementary food at recruitmentUse of supplements or medications that will affect the study outcomesIron deficiency (Hb < 105 g/L, serum (S-) ferritin < 12 μg/L) or any other biochemical abnormality discovered at the baseline examination that needs medical attention after decision by the study physician.Repeated non-adherence to key study procedures including anthropometric measurements, allergy, eczema and symptoms registrations.

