### Procedures

The baseline and 9, 12 and 18 mo. visits will take place at the Paediatric Research Unit at the Department of Clinical Sciences, Paediatrics, Umeå University Hospital.

At baseline, the researchers will establish that the participant fulfils all the inclusion criteria and none of the exclusion criteria, written informed consent will be collected if this has not been collected earlier and the parents will be given spoken and written information about the study and time to ask questions on the study procedures. The parents will also be given information on how to complete questionnaires and forms, whether on-line or on paper, how to upload photos and, if the participants are randomized to the ND group, how to access the on-line support forum, i.e. the closed Facebook group of the study. The participants will then be assessed according to the Figure including drawing blood samples and provided with a month’s supply of study products and recipes.

At ages 7 and 8 mo., the research nurse or dietician will have a telephone follow-up with the participants checking adherence, possible study related problems, supply and consumption of study products and symptoms registrations.

At age 9 mo. the participants will again come to the Paediatric Research Unit for measurements according to the Figure.

At ages 10 and 11 mo. the research nurse or dietician will have a telephone follow-up with the participants checking adherence, possible study related problems, supply and consumption of study products and symptoms registrations.

At 12 mo. of age, the participants will again come to the Paediatric Research Unit for providing samples according to the Figure. Further, the research nurse will do a home visit for anthropometric measurements, administration of the deuterium labelled water and the two videotaped tests, i.e. food acceptance test and the attention free play test.

At ages 13–17 mo., the research nurse or dietician will have a telephone follow-up with the participants checking adherence, possible study related problems, supply and consumption of study products and the symptoms registrations.

Finally, at 18 mo. of age, the participants will come for the final measurements of the study according to the Figure. The research nurse will again do a home visit for anthropometric measurements, administration of the deuterium labelled water and the two videotaped tests, i.e. food acceptance test and the attention free play test.

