### Withdrawal

The participants may withdraw from the study at any time by i) withdrawing consent, ii) through non-compliance (repeated failure to comply with study procedures) or if iii) the participant experiences adverse events requiring the participant to withdraw on advice of the research physician or by his/her own accord. If possible the researchers will explore the specific reasons why consent was withdrawn, type of non-compliance and which specific AEs that caused withdrawal. All reasons for withdrawal will be recorded. Participants who withdraw will not be replaced.

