### Power calculation and statistical analyses

The primary outcome of the study is body composition, i.e. fat mass measured by TBW. The body fat mass is on average 2.9 ± 0.6 kg at 12 mo. of age. In order to detect a difference in body fat of 0.24 kg between the intervention (ND) and control groups at 12 mo. of age (α = 0.05, power = 80%) with an attrition of 20%, we will need 125 participants per group.

Comparisons of differences in main outcomes between the ND and control groups will be the focus of the statistical analyses. The primary outcomes will be analysed according to the intention-to-treat principle when comparing the two study groups, but per protocol analyses will also be done. Both parametric and non-parametric tests will be used depending on the distribution of data. Possible effect modifiers and confounders will be included in the analyses as needed to explain group differences. Data on dietary intake will be converted to energy and nutrients through nutrient calculation software (Dietist NET, Kost och Näringsdata AB, Bromma, Sweden).

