## Discussion

The early diet has long-lasting effects on human health. Apart from breastfeeding, little is known about which infant diets would confer long-term health benefits. ND has several potential advantages in this respect, and studies in adults have shown favourable effects on metabolic- and cardiovascular disease markers and mortality similar to those gained through the Mediterranean diet. The present study, using ND as the basis for complementary foods but also reducing the total protein intake, improving fatty acid composition and expanding the introduction of fruits and vegetables into the diet of young children will add vital information in the quest to prevent obesity, dyslipidaemia, insulin resistance, type 2 diabetes, hypertension and cardiovascular disease. If the objectives of the study are reached it will thus serve to improve dietary recommendations to infants in Sweden and worldwide. Strengths of the study include individual randomization of the participants, use of well-validated methods of data collection and analysis and close follow-up and support to the participants through dedicated research staff. Possible limitations include difficulties of the families accepting and adhering to the ND, which may lead to higher drop-out rate in the intervention group. The focus on ND may also skew recruitment away from non-Nordic participants. However, this will most likely not affect the outcomes.

Through early intervention, i.e. already when complementary foods are introduced into the diet of the infant, we believe that we can initiate healthy food preferences from the earliest date, thus optimizing the long-term public health benefits. By adopting the concept of ND we will also add gastronomical aspects to the development of optimal complementary foods as well as support regional food production and contribute to a sustainable environment.

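### Repeated non-adherence is listed as an exclusion criterion although it can appear only after randomisation; removing randomised children on that ground would conflict with the intention-to-treat analysis

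*Protocol article*

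**What the plan says.** The last item under Exclusion criteria is "Repeated non-adherence to key study procedures including anthropometric measurements, allergy, eczema and symptoms registrations". The Withdrawal section treats the same kind of behaviour as a reason for leaving the study: "through non-compliance (repeated failure to comply with study procedures". Withdrawn participants are not replaced.

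Power calculation and statistical analyses states that "The primary outcomes will be analysed according to the intention-to-treat principle when comparing the two study groups", with per-protocol analyses in addition. The trial is sized to "detect a difference in body fat of 0.24 kg between the intervention (ND) and control groups at 12 mo. of age". Among possible limitations, the Discussion names "difficulties of the families accepting and adhering to the ND, which may lead to higher drop-out rate in the intervention group".

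On laboratory findings, the exclusion criteria give haemoglobin and ferritin cut-offs and add "any other biochemical abnormality discovered at the baseline examination that needs medical attention after decision by the study physician". The Randomisation section places randomisation at recruitment. At the baseline visit the Procedures section has eligibility checked and ND families told how to reach their forum; it continues: "The participants will then be assessed according to the Figure including drawing blood samples". Study products are handed out in that same step.

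**The concern.** An exclusion criterion decides who may be randomised. This one describes conduct during follow-up, so it can act only on children who already have an allocation. Its place in the eligibility list invites the reading that such a child was never properly in the trial and may be dropped from the analysis. The Withdrawal section classifies the same event as discontinuation, which has a different consequence for the analysis set.

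The protection given by randomisation for the fat-mass comparison is at stake. If removal is more frequent in one arm and is related to fat mass, the children left in the two arms are no longer comparable. The article itself allows for unequal loss. There is also a route by which the arm could influence the triggering behaviour: only ND families have the closed forum, and the Parental support section says that it may be used to remind families to return questionnaires.

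A lesser concern is that baseline laboratory results may reach the physician after allocation, when part of the decision to exclude is discretionary.

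**Working it through.** **1. Timing of the non-adherence criterion.**
- Randomisation: when the parents want to start complementary food, at 6 months at the latest (Participants and recruitment).
- Anthropometry after baseline: 9, 12 and 18 months.
- Allergy symptoms and eczema score: 9, 12 and 18 months.
- Symptom forms: returned monthly during follow-up.

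Repeated failure on these items needs at least two missed occasions, nearly all of which fall after randomisation. The item cannot work as an entry criterion.

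**2. The planned sample size.** Inputs from the power section: difference 0.24 kg, SD 0.6 kg, α = 0.05 (two-sided assumed), power 80%, attrition 20%.
- Normal approximation: n = 2 × (1.96 + 0.84)² × 0.6² / 0.24² ≈ 98.1, so 99 per arm; 99 / 0.8 = 123.75, so 124.
- t-test: 99.08, so 100 per arm; 100 / 0.8 = 125.

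The stated 125 per group reproduces, with 100 evaluable per arm and power 80.7% (t-test 80.4%).

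**3. Power if removals come on top of the 20% attrition.** Evaluable per arm = 125 × 0.8 × (1 − e), with the extra loss e equal in both arms (normal approximation):
- e = 2%: 98 per arm, power 80.0%
- e = 5%: 95 per arm, power 78.7%
- e = 10%: 90 per arm, power 76.5%

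If the removals are already part of the 20%, nothing is lost.

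**4. What selective removal could do.** Suppose that a fraction f of the ND arm only is removed, and that these children average d kg more fat mass than those retained. The retained ND mean is then lower than the full ND mean by f × d. Neither f nor d stands in the article; the values below are assumptions that show the range. Type I error takes no true effect, 100 × (1 − f) ND children and 100 controls.
- f = 5%, d = 0.3 kg: 0.015 kg, 6% of 0.24 kg, type I error 5.3%
- f = 10%, d = 0.3 kg: 0.03 kg, 12.5%, type I error 6.4%
- f = 20%, d = 0.6 kg: 0.12 kg, 50%, type I error 26.6%

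If d is negative, or if removal is heavier in the control arm, the sign reverses. With equal removal of similar children in both arms the bias is nil.

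**5. The laboratory criterion.** Randomisation at recruitment, together with a baseline visit that combines arm-specific instructions, the blood draw and product supply, makes it probable that results follow allocation. Yet the Procedures section also has every exclusion criterion checked at baseline, and Study design and interventions puts randomisation after recruitment. No sentence fixes the order. Baseline blood precedes the diets, so exclusion on it that disregards the arm has expected bias zero and costs only numbers.

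**The case against.** The strongest reply is that the criterion concerns measurements and registrations, not the diet. ND families use the products at their own discretion and the recipes and jars as they wish, and nothing in the article makes low use of them a ground for removal. A family that repeatedly misses measurements produces missing data under any label. This stands, and it limits the concern. A reader might infer that families who struggle with the diet will be taken out of the ND arm and that the result will therefore lean towards the hypothesis. The text does not support that: the Discussion says only that drop-out may be higher, and does so in connection with accepting and adhering to the diet.

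Secondly, no sentence says that excluded or withdrawn children leave the ITT analysis, and full definitions of analysis sets may stand in a plan that is not shown. This also stands. It would go too far to say that the ITT comparison becomes one of compliant families. What remains is that the article files a follow-up event as an exclusion criterion and says nothing to keep such children in.

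Thirdly, a reader might infer that the laboratory exclusions can act only after randomisation and also select on compliance. The order is probable but not stated, and values taken before the diets cannot select on compliance or on response to them. The haemoglobin and ferritin cut-offs are fixed, and the article says that researchers are blinded. Only the discretionary clause leaves room for a decision influenced by the arm, since nothing expressly requires that decision to be made without knowledge of it.

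**Conclusion.** The point holds in a limited form. Repeated non-adherence is misplaced among the exclusion criteria and appears again as a withdrawal route. Applied as written to randomised children, it conflicts with the ITT analysis. It may bias the fat-mass difference because the article allows for unequal drop-out, but neither the size nor the direction can be derived from the document. The 0.015 to 0.12 kg range rests wholly on assumed values of f and d and on removal in the ND arm alone. The loss of power is modest: down to 76.5% if 10% more are lost in each arm beyond the planned attrition, and none if the removals fall within it.

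The laboratory criterion is a secondary matter of unclear order, with a narrow risk confined to the discretionary decision.

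**What to change.** - Delete the non-adherence item from the exclusion criteria, and stop using non-compliance as a reason to end follow-up.
- Continue to invite non-adherent children to the 12- and 18-month outcome visits where consent allows.
- State that all randomised children stay in the ITT set, and that non-adherent children are left out of the per-protocol analysis only.
- Report any post-randomisation exclusions by arm, with reasons.
- Reconcile the Randomisation and Procedures sections on whether baseline laboratory results precede allocation. Keep children already randomised who meet the laboratory criterion in the ITT set, and have any discretionary exclusion decision made without knowledge of the arm. Medical care remains with the physician.

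Recruitment ended in February 2018 with 250 children, so the release of allocation can no longer be changed. Data collection runs to February 2019, so follow-up of remaining children, the analysis-set wording and the reporting can still be put right. The cost is protocol wording and invitations to visits already scheduled. The ITT effect may also be slightly smaller than the effect among compliers.
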